### Procedure

The RCT will involve the 120 adults being randomly allocated to either a HRV-F group or a no-treatment control group. Both groups will be similarly assessed over a period of 12-months, that is, at baseline, 10 weeks post-baseline (immediately after the HRV-F treatment for the intervention group), and at 6 and 12-month post-baseline. To test the feasibility of the RCT, the first 10 RCT participants with SCI who meet inclusion and exclusion criteria (5 in the HRV-F and 5 in the control arm) will be monitored for adherence to the HRV-F therapy and assessment, and for any barriers to the intervention and control group membership. The implementation study will involve conducting a mixed methods approach (qualitative and quantitative) to establish how best to translate HRV-F interventions into the community.

### Data management

After recruitment, participants will be de-identified and given a generated code. All data will be stored on a secure online platform called Research Electronic Data Capture (REDCap) [36]. Participants will enter their responses to the online interview/assessment using their personal REDCap link after being given instructions on how to complete. Participants not wanting to enter responses online will complete by face-to-face or telephone assessment with a member of the research team, who will then enter the data onto REDCap. The implementation phase participants will also be de-identified and data from the surveys and interviews will be entered into REDCap for further analysis.

### Randomization and blinding

RCT participants will be randomized to either the HRV-F group (*N* = 60) or to the no-treatment control group (N = 60) following a stratified randomization procedure. The randomisation allocation ratio is 1:1, while controlling for covariate level of injury (at and above T3 versus below T3). The randomization sequence will be computer generated via RAND function in Microsoft Excel by an independent person and then be uploaded into REDCap. Once the participant is recruited and completed the baseline assessment, then the assessor will inform the team members who are conducting the intervention. The researcher will then randomize a participant via pre-defined randomization sequence in REDCap (see Fig. 1). Team members responsible for recruitment, assessment and analysing the data will be blinded to group allocation. However, the researcher conducting the intervention as well as the participants will be aware of group allocation given it is not possible to blind them to the HRV-F versus control conditions.

**Fig. 1 Fig1:**
[figure not shown]
Showing participant allocation to the HRV-F versus Control conditions

### Setting

Participants living in the community will be recruited from outpatient clinics of the two participating sites, that is, Royal North Shore Hospital (RNSH) and Royal Rehab, NSW, or they will approach the research team after viewing study advertisements posted at targeted social and commercial media outlets. Assessment and the HRV-F intervention will only be conducted at the RNSH campus in which the testing laboratory, a dedicated air-conditioned laboratory, is situated. Participants in the HRV-F group will also complete some treatment components in their home setting. The implementation phase participants from the SSCIS Network will be asked to complete an online survey. The SSCIS Network members include clinicians, consumers, government policymakers and representatives from non-government organisations. Ten semi-structured interviews will be conducted via telephone with health professionals who have delivered the HRV-F intervention, or who would deliver the HRV-F if it was introduced into standard practice.

### HRV-F protocol and rationale

#### Rationale

HRV-F is designed to improve autonomic and neurocardiac functioning using computer-based feedback of HRV and controlled diaphragmatic slow breathing around 3–7 breaths per minute. One goal of HRV biofeedback is to stimulate the baroreflex and enhance respiratory sinus arrhythmia (RSA), which involves fluctuations in heart-beat intervals linked with respiration, associated with variations of the parasympathetic cardiac signal [37]. That is, cognition and brain neural activity to adhere to a paced respiration rate and depth, evoking resonant frequency changes to RSA in LF HRV and Total HRV power (in the spectral bands). RSA amplitude (peak-to-trough heart rate difference across the breathing cycle) is contingent with slow breathing [37] and establishing resonant breathing frequency (generally lying between 4 and 7 breaths per minute), identifies the breath rate that is associated with largest gains in RSA and baroreflex activity [37]. Slow breathing rates, and especially breathing at the resonant breath rate, optimally stimulates the baroreflex, resulting in increased RSA and HRV, which is believed to be associated with healthy autonomic and cardiovascular systems [37].

#### Resonant frequency

A central goal of HRV-F, therefore, is to establish a participant’s resonant breath rate [14, 19, 37]. Participants utilize feedback of their HRV in exercises to control their autonomic activity using dedicated biofeedback technology and software (ProComp 2 HRV Systems; Thought Technology, Ltd., Canada, www.thoughttechnology.com). In HRV-F, participants initially use this feedback technology to determine their unique resonant breathing rate, which is established over a period of 15 min while reducing their breath rate by 0.5–1 breaths per minute (BPM), and depending on a participant’s initial resting BPM, gradually decreasing BPM down to 4 or 5 BPM over the 15-min. Once participants have identified their unique resonant breathing frequency, they then proceed to perform varied resonant breathing exercises over the 10-week period. The protocol is shown in Fig. 2.

**Fig. 2 Fig2:**
[figure not shown]
Shows flow of HRV-F intervention sessions over 10 weeks

#### HRV-F training

Ten sessions of formal HRV-F training will be completed over the 10-week intervention. These will involve a mixture of six face-to-face formal sessions (2-h duration each) in the research laboratory and four online/telephone sessions (at-home sessions, up to 1-h duration). Face-to-face HRV-F sessions will be conducted in groups of three participants. However, it is expected that individual sessions will occur given risk of sickness in this population. Self-management strategies will be introduced throughout the 10 weeks of the program, including self-monitoring of mood, anxiety, breath rate, pain/fatigue level and sleep quality, as well as visualisation strategies to be used in conjunction with resonant breathing exercises.

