### Power analyses

For the primary outcome measures, assuming an α = 0.05, a small to moderate effect size of 0.3 (based on results from studies in other conditions), with 2 groups (HRV-F and control) of 50 in each group and four assessment periods, estimated statistical power is 0.99 [67]. To allow for reduced participant numbers due to loss to follow-up, sickness, death, or unwillingness to continue, we will recruit up to 120 participants.

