### Statistical methods

Descriptive statistics will be generated for all relevant primary and secondary outcomes at all time-points. Linear mixed models for repeated measures analyses will be used to determine the effectiveness of the HRV-F intervention in autonomic function/HRV and cerebral blood circulation in basal cerebral arteries blood flow. Secondary analyses will determine whether improvements occur in factors such as mental health, cognitive function and sleep associated with the HRV-F intervention. All analyses will be adjusted for factors suspected to confound results, such as education and relevant baseline scores. Latent class mixture modelling will be used to determine trajectories for primary and selected secondary measures like anxiety, depressive mood and quality of life. Missing data will be managed using the linear mixed models, for example, through fitting maximum likelihood estimations generating asymptotically unbiased parameter estimates [68]. Data analyses will be performed using packages such as Statistical Package for the Social Sciences (SPSS version 27, SPSS inc., Chicago, Illinois, USA).

For the implementation study, in which qualitative analyses will also be used, the data will be analysed using valid qualitative packages. Grounded theory, an inductive technique of interpreting the recorded data about the perceptions of the HRV-F and its translation, will be the basis for reaching conclusions about how best to implement and translate the treatment.

For cost-effectiveness, descriptive statistics will be calculated to determine costs and QALYs. The robustness of the costing data will be examined through sensitivity analyses. As in standard economic assessments, costs acquired in this study will likely be skewed, so nonparametric bootstrap methods will potentially be used for testing hypotheses tests and interval estimation. A threshold ICER for Australia will be used to assess value for money.

The ICER will be calculated as per equation (eq. 1) below, that is, the incremental cost per increase in time and frequency domain parameters and as incremental cost per QALY gained in the intervention compared to the controls, in the cost-utility analysis.

1$$ \mathrm{ICER}=\frac{\mathrm{Cost}\ \mathrm{of}\ \mathrm{intervention}\hbox{-} \mathrm{Cost}\ \mathrm{of}\ \mathrm{control}}{\mathrm{Outcome}\ \mathrm{of}\ \mathrm{intervention}\hbox{-} \mathrm{Outcome}\ \mathrm{of}\ \mathrm{control}} $$

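### HRV-F is delivered in groups of three and the control condition is not; the stated mixed model and power calculation make no allowance for this, so standard errors will be somewhat too small if outcomes correlate within groups

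*Protocol article*

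**What the plan says.** Under HRV-F training, the Protocol article plans ten formal sessions: six face-to-face sessions of two hours and four at-home sessions of up to one hour by telephone or online. On the former it says "Face-to-face HRV-F sessions will be conducted in groups of three participants". It then qualifies this: "it is expected that individual sessions will occur given risk of sickness in this population". How often that will happen is not stated, nor whether a group keeps the same members across its six sessions.

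The Control group protocol section gives controls reading material and a brief weekly call and describes no grouping. Allocation is individual: "The randomisation allocation ratio is 1:1" (Randomization and blinding).

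Statistical methods says "Linear mixed models for repeated measures analyses will be used to determine the effectiveness of the HRV-F intervention", with adjustment for factors such as education and baseline scores. Repeated measurement is the only source of correlation mentioned, and the random-effects structure is not given. Power analyses works from "assuming an α = 0.05, a small to moderate effect size of 0.3" and continues "with 2 groups (HRV-F and control) of 50 in each group and four assessment periods, estimated statistical power is 0.99". The only allowance added is for loss of participants: "we will recruit up to 120 participants". No ICC or design effect appears.

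**The concern.** Participants trained in the same trio share sessions, peers and whoever delivers the training. The training also includes self-monitoring of mood, anxiety, pain, fatigue and sleep, which are close to several self-reported secondary outcomes. If this makes outcomes within a trio more alike, the HRV-F arm mean varies more than 60 independent participants would imply, while the control mean does not. Individual randomisation does not remove this, because the correlation arises after allocation.

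A mixed model whose only random structure is at participant level would then give intervals for the treatment effect that are too narrow and a type I error above 5%. There is also a practical issue of timing: who trained with whom has to be recorded as the sessions happen. If it is not, no later analysis plan can model it.

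**Working it through.** **Inputs from the Protocol article.** Alpha 0.05, effect size 0.3, 50 per arm, four assessments, power 0.99, recruitment up to 120 (Power analyses); 60 per arm, 1:1 (Randomization and blinding); group size k = 3, HRV-F arm only (HRV-F training, Control group protocol).

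**Assumed, because the documents do not give them.** The ICC within a treatment group (0.05, 0.10, 0.20); a two-sided test; the correlation ρ between repeated measurements; and the metric of the effect size, read here as Cohen's f.

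**Step 1: the plan's own power.** With N = 100 and m = 4 in a repeated-measures ANOVA, f²·N·m = 0.09 × 100 × 4 = 36.

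- Group-by-time: λ = 36/(1 − ρ), df 3 and 294. At ρ = 0.5, λ = 72 and power is about 1.00.
- Between groups: λ = 36/(1 + 3ρ), df 1 and 98. At ρ = 0.3, λ = 18.9 and power is 0.991. At ρ = 0.5, λ = 14.4 and power is 0.964.

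The stated 0.99 is therefore reproducible on this reading, without any clustering.

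**Step 2: clustering in one arm.**

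- Design effect in the HRV-F arm: DE = 1 + (k − 1) × ICC.
- With equal arms, the variance of the difference is multiplied by V = (1 + DE)/2.
- The true standard error is √V times the naive one, so the naive one is too small by 1 − 1/√V.
- Actual type I error of a nominal 5% test = 2 × [1 − Φ(1.96/√V)].

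Everyone always in threes:

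| ICC | DE | V | True SE above naive | Naive SE too small by | Type I error |
|---|---|---|---|---|---|
| 0.05 | 1.10 | 1.05 | 2.5% | 2.4% | 5.6% |
| 0.10 | 1.20 | 1.10 | 4.9% | 4.7% | 6.2% |
| 0.20 | 1.40 | 1.20 | 9.5% | 8.7% | 7.4% |

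A simulation of 100,000 trials, with 20 groups of three (60/3) against 60 independent controls, gave type I errors of 5.5%, 6.0% and 7.4%. At ICC 0.01 the formula gives 5.1%, and at ICC 0 nothing changes.

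**Step 3: dilution.** If absences reduce the effective group size to two, DE is 1.05 / 1.10 / 1.20, V is 1.025 / 1.05 / 1.10, and type I error is 5.3% / 5.6% / 6.2%.

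**Step 4: effect on power.** Dividing λ by V at f = 0.3, ρ = 0.5 and 50 per arm, between-group power goes from 0.964 to 0.948 at ICC 0.10 (λ = 14.4/1.10 = 13.1) and to 0.929 at ICC 0.20 (λ = 14.4/1.20 = 12.0). Group-by-time power stays at about 1.00 up to ICC 0.30.

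**The case against.** The strongest reply is that this treats silence as an error. A reader might infer that the planned model assumes all participants independent and that its standard errors are therefore too small. The article does not say that. It gives no random-effects structure, a linear mixed model is exactly the class that can carry a group term, and such detail is often left to an analysis plan. That stands, so the point can only be conditional: the described plan does not account for the grouping, and the harm follows only if the ICC is positive. What does not fall away is that the article itself fixes one-arm group delivery, the model family and a sample size without clustering, and that membership must be captured during delivery. The article lists no such data item, although the full protocol may.

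The second reply is that the clustering is weak. Individual sessions are expected. Four of the ten formal sessions are at home. Each participant trains at an individual breathing rate, and home practice of two 20-minute sessions a day for 70 days comes to about 47 hours, against 12 hours face-to-face. This also stands and argues for the lower end of the range. Still, 12 of at most 16 hours of formal training, 75% or more, are planned as group time.

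Third, the primary outcomes are instrument recordings taken by blinded assessors, so shared influence is likelier in the self-reported secondary outcomes. That is a fair judgement, though blinding does not remove a correlation that the training itself produces.

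Finally, one might suspect a further deliverer effect. The documents do not say how many people deliver HRV-F, so its size cannot be assessed, and with a single deliverer it could not be estimated.

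**Conclusion.** The point holds in conditional form. The delivery described is partially nested, and neither the stated analysis nor the power calculation allows for it. Over assumed ICCs of 0.05 to 0.20, type I error would be 5.6% to 7.4% with full trios and 5.3% to 6.2% at an effective size of two. These figures rest on equal arms, a positive ICC that the documents do not supply, and a fitted model with participant-level correlation only. The effect is modest and probably greatest for self-reported secondary outcomes. A reader might also infer that the power of 0.99 is invalidated; Step 4 does not support that, since the change is small on the reading that reproduces the figure.

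**What to change.** 1. At each face-to-face session, record in REDCap the session group attended, or that the session was individual, and who delivered it.
2. Add to the mixed model a random effect for the assigned treatment group in the HRV-F arm only, with controls and individually treated participants as singletons, and use small-sample degrees of freedom. Make this the main analysis or at least a prespecified sensitivity analysis.
3. Report the estimated ICC with the results.

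The cost is an extra identifier field (two with the deliverer), an added model term and slightly wider intervals. With about 20 small groups the group variance may be estimated at zero. The plan should say in advance that the group term then drops out. If arm-specific residual variances are fitted as well, those would remain, so the result would not be exactly the model now described.

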#### Home practice

Homework related to HRV-F will be assigned and a diary used by participants to log homework activities. Homework activities will include (i) resonant breathing exercises as taught in the face-to face sessions; (ii) measuring HRV each day of the 10 weeks using phone-based apps; (iii) self-monitoring of mood, anxiety, breath/heart rate, pain, fatigue and sleep; (iv) maintaining a log of homework activities, and (v) visualisation strategies to enhance their self-regulation of HRV and breathing. Participants will be asked to practise resonant breathing exercises in the home environment, twice a day for around 20 min per session and once a week over the 10 weeks, a team member will provide telephone support. Phone apps will be used to record HRV data and determine adherence, as well as daily/weekly progress. All HRV-F participants will be given a total of $200 Australian in the form of eGift cards throughout the treatment program ($50 at initial and $50 at 10 weeks) and a final $100 after the 12-month assessment.

### Control group protocol

Control participants will receive the same assessment regime as the HRV-F participants. Controls will receive reading material and a brief telephone call each week in the 10-week period to establish their continued participation. Controls will receive similar payment to the intervention group.

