	ADFSCI questionnaire	In-person		**✓**	**✓**	**✓**	**✓**		
Cerebral basal artery blood flow	Doppler assessment – Long term	In-person		**✓**		**✓**	**✓**		
Neurophysiological function	Continuous BP	In-person		**✓**	**✓**	**✓**	**✓**		
	EEG	In-person		**✓**	**✓**	**✓**	**✓**		
	NIRS	In-person		**✓**	**✓**	**✓**	**✓**		
	EOG	In-person		**✓**	**✓**	**✓**	**✓**		
	Skin conductance, BVP, respiration and temp	In-person		**✓**	**✓**	**✓**	**✓**		
Secondary health conditions	SCI-SCS	In-person and online		**✓**	**✓**	**✓**	**✓**		
Cognitive function	NUCOG	In-person and online		**✓**	**✓**				
	Stroop test	In-person and online		**✓**	**✓**				
Psychological/mental health function	GADS	In-person and online		**✓**	**✓**	**✓**	**✓**		
	PHQ-9	In-person and online		**✓**	**✓**	**✓**	**✓**		
Psychosocial function	ISCoS pain questionnaire	In-person and online		**✓**	**✓**	**✓**	**✓**		
	FSS	In-person and online		**✓**	**✓**	**✓**	**✓**		
	PSQA	In-person and online		**✓**	**✓**	**✓**	**✓**		
	PCS	In-person and online		**✓**	**✓**	**✓**	**✓**		
Personal factors	*CD-RISC2 Short Form*	In-person and online		**✓**	**✓**	**✓**	**✓**		
Quality of life	*EQ-5D-5L*	In-person and online		**✓**	**✓**	**✓**	**✓**		
Participation and disability	*WHODAS domain – participation items*	In-person and online		**✓**	**✓**	**✓**	**✓**		
Consumer perception and satisfaction	Self-reported perception of change and satisfaction	In-person and online			**✓**				
Costs for Economic evaluation	Self-reported direct and indirect costs	Diaries (up to 12 m)						**✓**	
Adverse events	*Self-monitoring of Adverse events*	Diaries (up to 12 m)						**✓**	
Self-monitoring *of mood, breath rate, pain, fatigue and sleep quality*	*Numeric rating scale (0 to 10)*	Diaries (up to 12 m)						**✓**	
**EXPLORATORY OUTCOMES**	**OUTCOME MEASURE**	**Mode of data collection**							
Personal factors	*WHO ASSIST*	In-person and online		**✓**	**✓**	**✓**	**✓**		
	*COPE inventory – brief*	In-person and online		**✓**	**✓**	**✓**	**✓**		
	*ADAPSS – Short-form*	In-person and online		**✓**	**✓**	**✓**	**✓**		
	*MSES*	In-person and online		**✓**	**✓**	**✓**	**✓**		
Psychological/mental health function	PTSD Checklist 5	In-person and online		**✓**	**✓**	**✓**	**✓**		
Psychosocial function	SSQ6	In-person and online		**✓**	**✓**	**✓**	**✓**		
	Berlin Questionnaire	In-person and online		**✓**	**✓**	**✓**	**✓**		
Environmental factors	*Care, family and compensation status questionnaire*	In-person and online		**✓**	**✓**	**✓**	**✓**		

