### Adverse events

HRV-F is a low risk self-regulation intervention. It is unlikely to result in adverse events caused by the intervention or the devices used in the study. To monitor possible adverse events the following will occur: (a) A detailed record of all related and unrelated adverse events will be documented and kept in a locked cabinet or online in a password protected file. (b) The impact of each event on participant safety or on trial conduct will be clarified. (c) Assess and categorise the safety reports received from investigators. (d) Report all suspected unexpected serious adverse reactions. (v) Report to the sponsor (The University of Sydney) within 24-h of becoming aware of any serious adverse events. (vi) Report to the sponsor all safety critical events and any additional requested information relating to reported deaths.

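### The adverse-event record is open to events from any source, and in the 10 treatment weeks the HRV-F arm has extra staff contact that can feed it, so a between-arm harms comparison drawn from that record can be biased

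*Protocol article*

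**What the plan says.** All references are to the protocol article.

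- **Scheduled source.** Table 1 (Physiological assessment) lists "Self-monitoring of Adverse events" as a diary item, completed fortnightly for up to 12 months and shown for the whole RCT, not by arm. The short section on health-related cost, adverse events and self-monitoring also names the fortnightly diary. The Control group protocol adds that "Control participants will receive the same assessment regime as the HRV-F participants".
- **Safety record.** The Adverse events section states: "A detailed record of all related and unrelated adverse events will be documented". It also provides for assessing safety reports sent in by investigators. Neither item is tied to the diary.
- **HRV-F contact.** Under HRV-F training, "Ten sessions of formal HRV-F training will be completed over the 10-week intervention". These are "six face-to-face formal sessions (2-h duration each) in the research laboratory and four online/telephone sessions", the remote ones lasting up to 1 h. Under Home practice, "once a week over the 10 weeks, a team member will provide telephone support".
- **Control contact.** "Controls will receive reading material and a brief telephone call each week in the 10-week period to establish their continued participation".
- **Blinding.** Under Randomization and blinding, the researcher who delivers the intervention and the participants know the allocation.

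**The concern.** The diary gives both arms the same chance of having an event recorded. The safety record does not clearly do so, because it accepts events from any contact and the arms differ in contact during the 10 weeks. HRV-F participants regularly meet staff who know their allocation. The HRV-F training section itself expects illness to affect group attendance, so those staff will sometimes learn of an illness because a session had to be rearranged. Controls have no matching occasion, and the one stated purpose of their call is not a health enquiry.

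If arms are compared on that record, an intervention without harm could appear to cause extra events. Conversely, a real excess could be dismissed as a product of closer contact. The annual Data Monitoring Committee review of safety would face the same ambiguity. The Control of bias section covers selection, performance and attrition, but not unequal detection of harms. A later analysis cannot restore control events that nobody asked about.

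**Working it through.** The protocol article gives no adverse-event rate and no sample size for harms, so there is no figure to reproduce. The check counts contacts, compares the sources, and then illustrates the possible size.

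**1. Contact in the 10 weeks (HRV-F training, Home practice, Control group protocol)**

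- HRV-F session time: 6 × 2 h + 4 × up to 1 h = up to 16 h.
- HRV-F contacts: 10 sessions + 10 support calls = up to 20. If the support calls coincide with the four remote sessions, 20 − 4 = 16.
- Control: 10 brief calls.

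**2. Sources common to both arms**

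- Adverse-event diary: 10/2 = 5 fortnightly entries in the 10 weeks and 52/2 = 26 in 12 months.
- SCI-SCS and ADFSCI at baseline, 10 weeks, 6 months and 12 months. The SCI-SCS asks about the last 3 months, so its week-10 administration spans the treatment period.

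**3. Source found in one arm only**

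The ten HRV-F sessions. The weekly calls exist in both arms, but their stated purposes differ: support in one, continued participation in the other.

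**4. Illustration with equal true risk.** All values here are assumptions; none is in the document. Let *s* be diary sensitivity in both arms, and let *e* (HRV-F) and *c* (control) be the share of diary-missed events that other contact recovers.

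Recorded ratio HRV-F : control = [s + (1 − s)e] / [s + (1 − s)c]

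| Diary sensitivity s | e = 0.5, c = 0 | e = 0.5, c = 0.25 |
|---|---|---|
| 0.5 | 0.75/0.50 = 1.50 | 0.75/0.625 = 1.20 |
| 0.7 | 0.85/0.70 = 1.21 | 0.85/0.775 = 1.10 |
| 0.9 | 0.95/0.90 = 1.06 | 0.95/0.925 = 1.03 |
| 1.0 | 1.00 | 1.00 |

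If *e* = *c*, or if only diary events are compared (s/s), the ratio is 1.00 at every sensitivity.

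**5. Chance of a spurious HRV-F excess.** Take 60 per arm, a two-sided 5% test of two proportions (normal approximation), *e* = 0.5 and *c* = 0. Only a nominally significant excess in the HRV-F arm is counted, so the value without bias is 2.5%.

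| s | True risk 0.4: recorded risks | Chance | True risk 0.2: recorded risks | Chance |
|---|---|---|---|---|
| 0.5 | 0.30 vs 0.20 | 24% | 0.15 vs 0.10 | 13% |
| 0.7 | 0.34 vs 0.28 | 11% | 0.17 vs 0.14 | 7% |
| 0.9 | 0.38 vs 0.36 | 4% | 0.19 vs 0.18 | 3% |

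First cell worked through: the pooled proportion is 0.25; the null standard error is √(0.25 × 0.75 × 2/60) = 0.0791; the standard error under the recorded risks is √[(0.30 × 0.70 + 0.20 × 0.80)/60] = 0.0785; (0.10 − 1.96 × 0.0791)/0.0785 = −0.70, which corresponds to 24%.

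**The case against.** The strongest reply is that the adverse-event outcome is already symmetric. Table 1 defines it through a diary that both arms complete, and on that outcome the ratio is 1.00. The Adverse events section can be read as safety documentation and sponsor reporting only. The Statistical methods section describes no between-arm harms comparison, and its details may properly sit in an analysis plan that is not shown. This stands to the extent that no bias follows if only diary events are compared. It does not remove the point, because the wider record is a stated requirement, it has an additional route of entry in one arm, and that asymmetry arises when data are collected.

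A reader might go further and infer three things that the documents do not support:

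- **That harms will be found more completely in the HRV-F arm.** This depends on how complete the diary is and on which record is compared, and neither is stated. The control call has one stated purpose, but the text does not exclude health questions, and Control of bias promises regular communication with both groups.
- **That the diary is the only common source.** Both arms attend the same visits. The SCI-SCS covers conditions such as pressure ulcers and bladder problems, and the ADFSCI covers symptoms of hypo- and hypertensive episodes. These are not adverse-event forms, but they are equal enquiries about related conditions.
- **That a serious event in a control surfaces up to two weeks late.** Controls are telephoned weekly in this period, so a delay of that length is not established.

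**Conclusion.** The point holds in a limited form. Followed as written, the contact schedule and the source-unrestricted safety record give the HRV-F arm an additional route for capturing events during the 10 treatment weeks. A between-arm comparison that uses this record can be biased towards an apparent excess in the HRV-F arm.

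The size cannot be derived from the document. On the assumed values above, the recorded ratio runs from 1.00 to 1.50 and falls quickly as the diary becomes more complete. The conclusion rests on two conditions: the diary misses some events, and the comparison includes events from outside it. If either fails, this bias is absent. The differential contact covers about 5 of the 26 diary periods, although these are the weeks in which the treatment is given.

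**What to change.** - **Home practice and Control group protocol:** put one identical scripted question on adverse events and hospital admissions into the weekly call of both arms.
- **Adverse events:** state that the between-arm comparison uses the common sources, namely the diary and the scripted question. List events learned only in HRV-F sessions separately. They stay in the safety record and in sponsor reporting.

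The calls already take place in both arms, so the cost is about a minute per call and a sentence or two of protocol text. The recorded event count will rise slightly, which should be expected when totals are read.
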